| All potential subjects are referred from their primary urologists. They will be screened by a member of the study team, and the procedure will include:   1. a detailed history and clinical examination 2. screening investigations including FBC, renal panel. liver panel, thyroid function, urinalysis, PSA, hepatitis screen, chest X ray and ECG   These screening tests should be done after clinical eligibility is ascertained and the recruitment into the trial should occur within 4 weeks of screening.  In addition to the blood samples taken for screening, peripheral blood will be collected at the following occasions: (i) during trial entry, at the completion of ARN 509 therapy timed together with pre-operative blood tests, and after surgery timed together with post surgery PSA assessment About 50ml of blood will be taken at each venepuncture. A total of 175 ml for all study related blood tests is expected.  Voided urine about 150ml will be taken at the same timing as peripheral blood. A total of 470ml of urine will be expected to be collected.  These samples may be tested for the following, inclusive but not limited to proteomics, genetics and cytokines testing.  The samples will be retained at the end of the study by the investigator and stored in a secure room in SGH. Only the study team will have access to the study samples. In the event the samples are required to be transported outside SGH to a service provider, these samples will be coded.  The subject can withdraw consent to participate in the sample collection and/or for their samples to be retained at any time and still continue with the study.  Sample analysis is restricted to purposes of this study and not for future unknown usage. |
| Study Visits and Procedures |
| The following are scheduled during the intervention phase of the study:   1. week 0 where patients will receive ARN 509 2. week 4 after commencement of ARN 509 for clinical consult, physical examination and QoL outcomes 3. week 12 at completion of ARN 509 treatment, where clinical examination, blood investigations, QoL outcomes and adverse effects monitoring is performed 4. Standard of care surgery by week 16 5. Final visit at weeks 20-24 for a clinical examination, QoL outcomes, adverse effects monitoring and serum PSA assessment |
| Final Study Visit: |

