| An adverse event (AE) is any untoward medical occurrence in a patient or clinical investigation subject administered a pharmaceutical product and which does not necessarily have a causal relationship with this treatment.  A serious adverse event (SAE) or reaction is any untoward medical occurrence that at any dose:   - results in death - is life-threatening - requires inpatient hospitalisation or prolongation of existing hospitalisation - results in persistent or significant disability/incapacity or - is a congenital anomaly/birth defect - is a medical event that may jeopardize the patient and may require medical or surgical intervention to prevent one of the outcomes listed above.   Potential Discomforts, Side Effects, and Risks Associated with Apalutamide  The possible discomforts, side effects, and risks related to apalutamide treatment are not all known. Though, most side effects are not serious, some may be serious and may require treatment or additional testing. This section describes how frequently side effects occurred in subjects who were treated with apalutamide.  There may be risks with the use of apalutamide that are not yet known. You will be watched carefully during this study for any side effects. Sometimes during a study the sponsor or study doctor may learn new facts about the study medications. It is possible that this information might make you change your mind about being in the study. If new information is discovered, your study doctor will tell you about it.  Side effects may be mild or serious. All medicines have the potential to cause an allergic reaction. Some allergic reactions and side-effects may potentially be life threatening. If you do experience any side effects, your doctor may need to give you medicines to help lessen the side effect. Many side effects may go away soon after you stop taking thestudy medicine. In some cases, side effects can be serious or long lasting.  If you experience a side effect, your treating doctor may change your study drug doses in an effort to decrease or stop any side effects.If severe side effects do develop, you and your doctor may decide that it is in your best interest to stop taking part in the study. If you choose, you always have the right to withdraw from the study. In addition, you will be provided with the telephone numbers for people who can answer any questions about the study, your rights as a study participant and for you to report any side effects.  Risks and side effects that may be possibly related to apalutamide include:   | **Very Common (>10%)** | **Common (1-10%)** | **Very Rare ( < 1%)** | | --- | --- | --- | | Fatigue | Itching | Seizures | | Diarrhoea | Falls |  | | Nausea | Insomnia |  | | Vomiting | Increase in blood cholesterol |  | | Skin rash | Increase in blood triglycerides |  | | Abdominal pain |  |  | | Changes in thyroid function |  |  | | Taste alterations |  |  | | Constipation |  |  | | Decreased appetite |  |  | | Hot flashes |  |  | | Dizziness |  |  |   Seizures have been observed very rarely in patients taking part in apalutamide studies that are still blinded (blinded means that neither the doctor nor the patient knows whether the patient is receiving apalutamide or placebo). Your doctor will confirm that you have no history of seizures and will check throughout the study that you are not taking other medications that can increase your risk of seizures. Please inform your doctor of all medications you take and any changes in medications. If you think you might have had a seizure, or convulsion, or have lost consciousness (passed out), let your doctor know right away.  Some patients on apalutamide studies have developed a rash. The cause of the rash is not known. The rash may be confined to one area of your body or may involve your entire body. If you start to develop a rash on any part of your body, or if you develop any other symptoms that are worrisome to you, contact your study doctor right away.  The effect of the study drug on your semen is unknown. To avoid risk of drug exposure to your partner through the semen (even in men with vasectomies [tubes that carry semen from the testicles have been cut]), or cause harm to an unborn child, you must use a condom during sexual activity while on study drug and for 3 months following the last dose of study drug.  Apalutamide may cause harm to the unborn child. From when you start taking the study drug until 3 months after your last dose of study drug, you must use a condom and another effective method of birth control when you have sex with a woman of child-bearing potential. The type of birth control you use must be discussed with, and approved by, the study doctor before you begin the study. This is done to prevent pregnancy. If your partner becomes pregnant in the time between when you start taking the study drug until 3 months after your last dose of drug, you must tell the study doctor immediately.  Donation of sperm is not allowed during the study and for 3 months following the last dose of study drug.  You should advise your study doctor if you father a child while participating in the research project. The doctor will advise you on any appropriate medical attention for your partner should this be necessary. The sponsor may ask you and your partner to allow him/her to collect information about her pregnancy and the health of the baby. |

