| - - - 1. Safety Analyses   Drug related adverse effects will be graded according the CTCAE grading scale. All AEs reported will be graded according to scale and the prevalence calculated. |
| - - - 1. Interim Analyses   An interim analysis of outcomes will be performed when 50% accrual is completed.   - - - 1. Describe the types of statistical interim analyses, including their timing.   This will be performed when 50% accrual is completed, and will include:   1. safety outcomes analysis 2. study primary and secondary objectives as listed |
| **DIRECT ACCESS TO SOURCE DATA/DOCUMENTS** The investigator(s)/institution(s) will permit study-related monitoring, audits and/or IRB review and regulatory inspection(s), providing direct access to source data/document. **QUALITY CONTROL AND QUALITY ASSURANCE** The collected data will be compared with the source data ( patient case records). This will be cross checked by at least 2 members of the study team. The access to the data will also be maintained under lock and key and only accessible to the PI and co-PIs.  Evaluation of data quality is every 6 months.  The PI and co-investigators would perform the data and safety monitoring. **ETHICAL CONSIDERATIONS** This study will be conducted in accordance with the ethical principles that have their origin in the Declaration of Helsinki and that are consistent with the Singapore Good Clinical Practice and the applicable regulatory requirements.  This final study protocol, including the final version of the Patient Information and Informed Consent Form, must be approved in writing by the Centralised Institutional Review Board (CIRB) and regulatory approval from Health Sciences Authority (HSA), prior to enrolment of any patient into the study.  The principle investigator is responsible for informing the CIRB and HSA of any amendments to the protocol or other study-related documents, as per local requirement. |
| Informed Consent |
| The consent will be obtained after the patient is aware of his diagnosis and has consented to undergoing radical prostatectomy for prostate cancer.  Consent will be obtained by PI and co-PIs, and will be taken in the outpatient clinic. This is the most common location where patients are told of their diagnosis and counselled for surgery.  Patients will be told that their treatment and follow-up will not be influenced by their decision on enrolment into the study.  We will recruit English speaking patients. There will be no minors. |

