**List of Attachments**

| Appendix 1 | Study Schedule |
| --- | --- |
| Appendix 2  Table 1 | Blood Sampling Summary  Trial Flow chart |
|  |  |
| **Appendix 1 Study schedule**  Total n=30: Obtain informed consent.  Screen potential participants by inclusion and exclusion criteria.  Physical examination, ECG, Chest X-ray and screening investigations  QoL outcomes assessment  Visit 1  Prior to  Enrolment  Entry into trial  Blood and urine samples collected for translational research  Commence ARN 509 administration  Visit 2  Week 0  Follow-up assessments for drug related side effects  Physical examination  QoL outcomes assessment  Visit 3  Week 4  Follow-up assessments  (physical examination, blood tests (FBC, renal panel, urine tests, PSA levels), urinalysis and QoL outcomes)  (blood and urine samples for translational research)  Visit 4  Week 12  Standard of care surgery  Week 12-16  Visit 5  Week 20-24 | **Final Assessments**  Physical examination  Blood tests (PSA level)  Blood and urine samples for translational research  QoL outcomes |
|  |  |

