**Table 1. ARN 509 Phase II Investigator initiated trial Singapore General Hospital - Trial Flow Chart**

| Patients on treatment arm with ARN509 | | | | | | | |
| --- | --- | --- | --- | --- | --- | --- | --- |
| Trial Period | Screening | ARN 509 | | Follow-up (1) | Standard of care surgery | Follow-up (2) | Remarks |
| Week | -4 | 0 | 4 | 12 | 12-16 | 20-24 |  |
|  |  |  |  |  |  |  |  |
| **Administrative procedures** | | | | | | | |
| Informed consent for trial and biochemical research | X |  |  |  |  |  |  |
| Inclusion/ exclusion criteria | x |  |  |  |  |  |  |
| Subject identification card | x |  |  |  |  |  |  |
| Medical history |  |  |  |  |  |  |  |
| ECOG performance assessment | x |  |  |  |  |  |  |
| Concomitant medication review | x |  |  |  |  |  |  |
|  |  |  |  |  |  |  |  |
| **Clinic procedures** | | | | | | | |
| Full physical examination | X |  |  | X | x | x |  |
| Vital signs, Body mass index | x |  |  | X | x | x |  |
| 12 lead ECG | x |  |  |  |  |  |  |
| Chest X Ray | x |  |  |  |  |  |  |
| ARN509 administration |  | X | X | x |  |  |  |
| SOC surgery |  |  |  |  | x |  |  |
| Adverse Events monitoring |  | x | x | X | x | x |  |
| Assessment of surgical complications |  |  |  |  | x | x |  |
| Assessment of QoL outcomes (QLQC30, PR25 and SHIM) | x |  | x | x |  | x |  |
|  |  |  |  |  |  |  |  |
| **Laboratory procedures** | | | | | | | |
| FBC with differentials | X |  |  | x |  |  |  |
| Renal panel including calcium and phosphate levels | x |  |  | x |  |  |  |
| Liver panel | X |  |  | x |  |  |  |
| PSA levels | X |  |  | x |  | x |  |
| Urinalysis | X |  |  | x |  |  |  |
| Thyroid function test | X |  |  |  |  |  |  |
| Hepatitis and HIV status | X |  |  |  |  |  |  |

| Trial Period | | Screening | ARN 509 | | Follow-up (1) | Standard of care surgery | Follow-up (2) | Remarks |
| --- | --- | --- | --- | --- | --- | --- | --- | --- |
| Week | | -4 | 0 | 4 | 12 | 12-16 | 20-24 |  |
| **Protocol specific collection** | | | | | | | | |
| Blood | CTCs from peripheral blood |  | x |  | x |  | x |  |
| Plasma ( ctDNA, miRNA, exosomes) |  | X |  | x |  | x |  |
| PBMC genotypic analysis |  | X |  | x |  | x |  |
| Serum (biomarkers) |  | X |  | x |  | x |  |
| Urine | Urine (miRNA, exosomes) |  | X |  | x |  | x |  |
| Tissue | Pre-treatment prostate cancer tissue (needle biopsy)  (DNA, RNA, IHC, methylation status) |  | x |  |  |  |  |  |

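### Raised cholesterol and triglycerides are named as common apalutamide effects, but no visit measures lipids, so the trial cannot systematically ascertain them

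*Protocol*

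**What the plan says.** Section 7.1 (Definitions) tabulates effects possibly related to apalutamide by frequency. The common column, 1-10%, includes "Increase in blood cholesterol" and "Increase in blood triglycerides".

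The section on screening visits and procedures asks for "screening investigations including FBC, renal panel. liver panel, thyroid function, urinalysis, PSA, hepatitis screen, chest X ray and ECG". For week 12, Appendix 1 lists "blood tests (FBC, renal panel, urine tests, PSA levels), urinalysis and QoL outcomes"; Appendix 2 and Table 1 add a liver panel at that visit. At weeks 20-24 the only clinical laboratory test is PSA. The most detailed chemistry entry in Table 1 is "Renal panel including calcium and phosphate levels".

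Research blood and urine are also collected, for purposes described as "inclusive but not limited to proteomics, genetics and cytokines testing".

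The Safety Monitoring Plan (7.4) collects scheduled safety data by asking subjects about adverse effects they have experienced. The Safety Analyses (9.2) state: "All AEs reported will be graded according to scale and the prevalence calculated". The hypothesis is that the regimen is safe and feasible, and the general considerations in 9.2 say the analyses are meant to characterise outcomes as background for later trials.

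**The concern.** A rise in cholesterol or triglycerides, as named in the risk table, is a change in a blood level. Asking a man how he feels cannot establish or grade it; that takes a measurement, and attributing a change to the treatment period also takes a baseline. The schedule provides neither.

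The design makes this matter somewhat more. With no control arm, each man's own pre-treatment value is the only internal reference. A measurement that was never taken cannot be recovered by any later analysis, and the schedule of assessments belongs to the protocol, so the gap cannot be left to a statistical analysis plan.

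At stake is the completeness of the all-grade safety description. Two effects the protocol itself expects at a non-trivial rate fall outside what the trial can systematically observe. A later reader who sees no lipid events could take that as information about the drug when it only reflects that nobody was tested.

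**Working it through.** **Step 1. Is a lipid test scheduled anywhere?** The clinical laboratory tests in each place are:

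- Screening list: FBC, renal panel, liver panel, thyroid function, urinalysis, PSA, hepatitis screen. No lipid test.
- Appendix 1, week 12: FBC, renal panel, urine tests, PSA, urinalysis. No lipid test.
- Appendix 1, weeks 20-24: PSA. No lipid test.
- Appendix 2 and Table 1, screening: FBC, renal panel with calcium and phosphate, liver panel, PSA, urinalysis, thyroid function, hepatitis and HIV. No lipid row.
- Appendix 2 and Table 1, week 12: FBC, renal panel, liver panel, PSA, urinalysis. No lipid row.
- Research samples: circulating tumour cells, plasma, PBMC, serum biomarkers, urine. The list is open-ended, but no lipid assay is named.

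Scheduled lipid measurements per man: 0 before treatment and 0 on treatment.

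**Step 2. How many cases might there be?** Inputs: n = 30 (study population section) and a rate p between 0.01 and 0.10 (section 7.1). The value p = 0.05 is added as a point inside the band. Expected cases per effect = n × p. Chance of at least one case = 1 − (1 − p)^n.

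- p = 0.01: 30 × 0.01 = 0.3 cases; 1 − 0.99^30 = 0.26.
- p = 0.05: 30 × 0.05 = 1.5 cases; 1 − 0.95^30 = 0.79.
- p = 0.10: 30 × 0.10 = 3 cases; 1 − 0.90^30 = 0.96.

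**Step 3. What would a mistaken zero imply?** If someone later treated no reported lipid events as 0 of 30, the exact one-sided 95% upper limit would be 1 − 0.05^(1/30) = 0.095, or 9.5%. That would appear to exclude rates above 9.5%, although no man had been tested. The protocol does not plan such an entry; the calculation shows only why the gap should be declared.

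The protocol states no figure of its own on this point, so there is none to reproduce.

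**The case against.** The strongest reply is that nothing is contradicted. The risk table is written as disclosure to participants; it does not commit the trial to measuring each listed effect, and no objective concerns lipids. This stands, and it is why the point is an improvement and not an error in the plan.

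A reader might go further and infer that the trial will report these effects as absent whatever the drug does. The documents do not support that. The prevalence in 9.2 is calculated on reported events, and no table listing every named effect is planned. Other routes also exist. The screening list is introduced as inclusive, adverse events are recorded from consent to 28 days after the last dose, and concomitant medication is documented, so a lipid result or new lipid treatment from outside care could be captured. Such capture would be incidental and without a study baseline. It does not yield a valid prevalence, but it means the effects are unascertained, which is different from being reported as zero.

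Two other inferences are tempting. One is harm to the secondary objective on grade 3 or higher events; the 1-10% band is not split by grade, so no loss there can be shown. The other is a surgical risk from unrecognised raised lipids; the documents give no such link.

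It is also fair to say that the band comes without a population, duration or grade, and that 30 men give little precision: 3 of 30 has an exact 95% interval of about 2% to 27%. This limits what the added data could show. It does not justify a prevalence based on no measurement.

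Finally, thyroid change is arguably the clearer example. It is listed as very common (>10%) yet tested only at screening. That is a parallel gap in the same schedule and does not remove this one.

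**Conclusion.** The concern holds in a limited form. Two effects that the protocol names as common and possibly drug-related can be established only by a blood test that no visit includes. They are not systematically ascertained, and the all-grade prevalence in 9.2 cannot validly describe them.

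The size is modest: 0.3 to 3 expected cases per effect in 30 men, with a 26% to 96% chance of at least one. These figures assume that the 1-10% band carries over to 12 weeks of treatment in this population, that men are independent, and that all 30 would be measured. The range is wide because the band is wide.

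The primary objectives and the count of grade 3 or higher events are not shown to be affected.

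**What to change.** Add total cholesterol and triglycerides to the laboratory rows of Table 1 and Appendix 2 at screening and week 12, and bring the screening list and Appendix 1 into line. Blood is already drawn at both visits, so no new visit or venepuncture is needed. The cost is two routine assays at two time points, about 30 × 2 × 2 = 120 results in all, which is a small laboratory expense.

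If the tests are not added, put one sentence in the Safety Analyses stating that lipid effects were not assessed, and report no prevalence for them. Incidental lipid results recorded as adverse events can still be listed individually.

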| The potential direct benefits to participants include:  (i) better long term cancer control when there is synergism between neoadjuvant androgen receptor inhibition and radical surgery  (ii)  better understanding of the clinical efficacy of ARN509 in organ confined prostate cancer will potentially allow wider clinical indications for this new drug.  (iii) with better long term cancer control, there is a lower risk of recurrence and the need for future treatment including prolonged androgen deprivation therapy or radiation therapy  (iv) downstaging of disease in the prostate allows for higher probability of nerve sparing surgery which will lead to better functional outcomes of continence and potency  (v) the background information from this study may allow the study team to progress onto a multi-centre, double-blind, placebo controlled trial which will enhance the care of prostate cancer for patients  The indirect benefits to the participants include:  (i) better understanding of the biological response of human prostate cancer to ARN 509 which will potentially give insight to new therapeutic options |
|  |
| **STUDY POPULATION** |
| List The Number and Nature of Subjects to be Enrolled. |
| This will be a single centre study recruiting n=30 patients. Only male patients between 21-75 years of age will be recruited as this age range represents the surgical cohort predominant in our local practice. |
| Criteria for Recruitment and Recruitment Process |
| Suitable patients will be screened by the study team investigators and recruited in the outpatient clinics in the Singapore General Hospital. |
| Inclusion Criteria |
| The inclusion criteria include   1. those aged between 21 to 75 years of age with histologically diagnosed primary adenocarcinoma of the prostate gland within 6 months of recruitment 2. non-metastatic D’Amico intermediate to high risk patients undergoing radical prostatectomy as primary definitive therapy 3. no known hypersensitivity to the study drug 4. able to swallow study drug as whole tablets |
| Exclusion Criteria |

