| The exclusion criteria will include   1. presence of small cell, neuroendocrine or ductal differentiation at needle biopsy of the prostate gland 2. individuals with prior pelvic irradiation therapy for any form of pelvic malignancy 3. patients with psychiatric conditions requiring anti-psychotic therapy, or preventing the provision of informed consent 4. renal impairment with serum creatinine more than twice the upper limit of normal 5. Other prior malignancy less than or equal to 5 years prior to recruitment 6. ECOG performance status 2 or poorer |
| Subject Replacement |
| There will be an attempt to replace subjects who drop out of the study. |
| **STUDY DESIGN** |
| This is a single arm phase II study in a single centre in Singapore.  Upon recruitment, all patients will undergo oral administration of ARN 509 (apalutamide) 240mg once daily for 12 weeks. This is followed by standard of care radical prostatectomy within 4 weeks of the last dose of ARN 509.  The details of visits and research related activity schedule is listed in Table 1. |
| There will be no video recording of these procedures. |
| Randomisation and Blinding |
| There is no randomisation or blinding in this study. |
| Contraception and Pregnancy Testing |
| If the study subject is engaged with sexual activity with a woman of childbearing potential, he should use contraception in the time period during and up to 3 months after the last administered dose of ARN 509. |
| Study Visits and Procedures |
|  |
| Screening Visits and Procedures |

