| The final study visit is about 4-6 weeks after standard of care surgery, where clinical examination, QoL outcomes measurement, adverse effects monitoring and serum PSA will be ascertained. |
| Post Study Follow up and Procedures |
| A post study follow-up is planned only for individuals who have drug related adverse effects that are present at the initial study visit. These patients will be monitored until resolution of adverse effects. |
| **TRIAL MATERIALS** |
|  |
| Trial Product (s) |
| This information is provided in section 4 (Effects in Humans) of the Investigator’s brochure which is attached.  Apalutamide is not marketed in Singapore, and the use of the study drug will be followed as per protocol. |
| Storage and Drug Accountability |
| The product comes as 60mg tablet stored in high density polyethylene (HDPE) bottles with child-resistant closures (CRC) and tamper-proof heat induction seals.  They are to be stored at room temperature in lock and key. |
|  |
| **TREATMENT** |
| Rationale for Selection of Dose |
| Preceding phase I and II studies have determined a daily dose of 240mg is efficacious and safe ( See Investigator Brochure Section 4.2 and Appendix B.1) |
| Study Drug Formulations |
| They will be dispensed as tablets to be stored at room temperature. |
| Study Drug Administration |
| The study drug should be taken once in the morning with or without food. |
| Specific Restrictions / Requirements |
| The following drugs should be stopped during the study period when ARN 509 is being consumed:   - Aminophylline/theophylline -  Atypical antipsychotics (eg, clozapine, olanzapine, risperidone, ziprasidone) -  Buproprion -  Lithium -  Meperidine and pethidine -  Phenothiazine antipsychotics (eg, chlorpromazine, mesoridazine, thioridazine) -  Tricyclic and tetracyclic antidepressants (eg, amitriptyline, desipramine, doxepin,   imipramine, maprotiline, mirtazapine) |
| Blinding |
| Not applicable. |
| Concomitant therapy |
| All medications (prescription and over the counter), vitamin and mineral supplements, and / or herbs taken by the participant should be documented. |
|  |
| **SAFETY MEASUREMENTS** |
| Definitions |

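### Section 7.1 has the doctor confirm that there is no seizure history, but no eligibility criterion mentions seizures, and Table 1 schedules the medication check at screening only

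*Protocol*

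**What the plan says.** The risk text under section 7.1 (Definitions) is addressed to the participant. It lists seizures among effects possibly related to apalutamide, at a frequency below 1%, and says they have been seen very rarely in apalutamide studies that are still blinded. It then gives two safeguards, the second aimed at drugs liable to raise the risk of a seizure: "Your doctor will confirm that you have no history of seizures and will check throughout the study that you are not taking other medications". It also asks the participant to report his medications and any change in them.

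The operative parts of the protocol read as follows.

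- **Inclusion Criteria** (4 items): age and histology, D'Amico risk group, "no known hypersensitivity to the study drug", and ability to swallow the tablets.
- **Exclusion Criteria** (6 items): certain histological variants, prior pelvic irradiation, psychiatric conditions, renal impairment, other recent malignancy, and "ECOG performance status 2 or poorer".
- **Screening Visits and Procedures**: "a detailed history and clinical examination", plus laboratory tests, chest X-ray and ECG.
- **Appendix 1, first visit**: "Screen potential participants by inclusion and exclusion criteria".
- **Section 6.4**: "The following drugs should be stopped during the study period when ARN 509 is being consumed", followed by seven drug groups. Section 6.6 requires all medications to be documented, without saying when.
- **Study Visits and Procedures**: "week 4 after commencement of ARN 509 for clinical consult, physical examination and QoL outcomes". Appendix 1 describes the same visit as "Follow-up assessments for drug related side effects" together with a physical examination and quality of life.
- **Table 1**: concomitant medication review is marked at screening only.

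**The concern.** Section 7.1 describes a condition to be confirmed for each man. Eligibility, however, is decided from the inclusion and exclusion lists, and those lists say nothing about seizures. Two members of the study team could handle the same man differently. One who works from the lists enrols him. One who has read the participant-directed wording under Definitions would not be able to give the confirmation promised there. At stake is the exposure of a man with a seizure history to 12 weeks of a drug for which the protocol names seizures as a possible risk.

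The second issue is narrower. The check for drugs that raise seizure risk is promised for the whole study, yet the schedule attaches it to no visit during dosing. A barred drug started after screening could go unnoticed unless the patient volunteers it or a clinician happens to ask.

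**Working it through.** No calculation applies. The check is a comparison of texts, with counts.

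**1. Eligibility**

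- Criteria: 4 inclusion + 6 exclusion = 10.
- Criteria naming seizures, epilepsy or a predisposing condition: 0 of 10.
- The nearest item is the third exclusion. It covers psychiatric conditions that need anti-psychotic treatment or prevent consent, and it does not reach a man with a past seizure and no such condition.
- The gate is the list: Appendix 1 screens by the criteria, and Table 1 has a row for the inclusion and exclusion criteria at screening.
- The screening history can bring a past seizure to light, but no listed criterion says what to do with that answer. The only text that does so is the participant-directed sentence in section 7.1.

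Set side by side, a man with a past seizure who meets everything else passes 10 of 10 criteria and fails the confirmation in section 7.1.

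**2. Medication check in Table 1**

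The visit columns are weeks -4, 0, 4, 12, 12-16 and 20-24, so 6 in all. Two of them (weeks 0 and 4) are headed ARN 509.

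| Row in Table 1 | Columns marked | Count |
|---|---|---|
| Concomitant medication review | -4 | 1 of 6; 0 of the 2 ARN 509 columns |
| Medical history | none | 0 of 6 |
| Full physical examination | -4, 12, 12-16, 20-24 | 4 of 6 |
| Adverse Events monitoring | 0, 4, 12, 12-16, 20-24 | 5 of 6 |

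The week 4 descriptions in Study Visits and Procedures and in Appendix 1 name no medication review. The scheduled safety enquiries in section 7.4 concern adverse effects only.

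The other rows show how much weight a blank cell can bear. Medical history has no mark at all, although the screening text requires a history. The physical examination has no week 4 mark, although both visit descriptions include one. The single mark for medication review is therefore an inconsistency in the schedule. It does not show that no check during treatment is intended.

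**The case against.** The strongest reply is that silence is not permission. The criteria do not admit men with a seizure history; they merely omit the subject. Section 7.1 belongs to the same protocol, and the screening history supplies the means to apply it. On this view all that is missing is a repetition. It can be added that section 7.1 does not state what follows if a history is found, that the consent pages and the Investigator's Brochure are not at hand and may carry a restriction, and that the Potential Risks section says seizures were not observed in human studies at 240 mg daily, which is this trial's dose.

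Part of this stands. The safeguard is stated, a procedure that could serve it exists, and what staff would do in practice cannot be known from the protocol. It does not remove the gap. Screening is done against a list, and a condition that is absent from that list and present only in patient-directed wording under Definitions is easy to miss. The low frequency does not settle the matter either, since the protocol itself thought the risk sufficient to promise the confirmation.

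On the medication check the reply is stronger. The protocol already has a stop list for the dosing period, a duty to document all medications, a duty to check throughout the study, a request that patients report changes, and a week 4 consultation. The anti-psychotic exclusion overlaps two of the seven barred drug groups. Table 1 is unreliable in other rows, and marks may have been lost when the table was extracted from PDF. This part alone would be an editorial remark.

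**Conclusion.** The concern holds. Its weight rests on the eligibility gap: 0 of 10 criteria name seizures, so the list admits a man whom section 7.1 says must first be cleared. This inconsistency on a named drug risk should be corrected.

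The medication-review point is secondary and less certain. The rule and the duty exist, but the schedule ties them to no dosing visit (1 of 6 columns marked, 0 of the 2 headed ARN 509).

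The protocol gives no figure for how many of the 30 men might have a seizure history, so the number affected cannot be stated. The conclusion assumes that staff determine eligibility from the listed criteria, as Appendix 1 directs, and that Table 1 is reproduced faithfully; only the secondary point depends on the latter. The statistical design and the collection of adverse events are unaffected.

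**What to change.** 1. Add *history of seizure* to the Exclusion Criteria.
2. In Table 1, mark concomitant medication review at weeks 0 and 4, to be checked against the drug list in section 6.4, and say so in Study Visits and Procedures. The choice of these two visits is a judgement, since section 7.1 names none; they are the existing visits in the columns headed ARN 509. A week 12 mark is optional and would only record exposure, because dosing ends there.
3. While Table 1 is open, mark medical history at screening, where a past seizure would be found and where the screening text already requires a history.

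The cost is one exclusion line, three ticks (two for medication review, one for medical history) and a few words at existing visits, with no new visit or test. Men with a seizure history become ineligible, which section 7.1 already implies.
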